### Outcome measures

The primary outcome measure is time (in weeks) to recurrence of a mood (depressive/manic/hypomanic/mixed) episode. This will be assessed at each follow-up using the Longitudinal Interval Follow-up Evaluation (LIFE),^29^ an integrated system for assessing the longitudinal course of psychiatric disorders. The assessment will consist of a semi-structured interview, during which an interviewer uses the LIFE to collect detailed psychosocial, psychopathological and treatment information for the follow-up interval. The weekly psychopathology measures are ordinal symptom-based scales with categories defined to match the criteria of DSM-5. Additional secondary measures are listed in Appendix 3.

All scales (both self-report and clinician-rated) will be administered using a tablet, to allow results to be safely and instantly loaded to the study database, with paper versions available if there are technological difficulties. All scales will be translated into Urdu and back-translated into the original language. Most have been used in previous studies in Pakistan, including our pilot.^24^

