### Study procedures

We have seven major recruitment centres, each with multiple out-patient psychiatric units. There are five recruitment sites in Karachi, three in Lahore and one each in Multan, Rawalpindi, Peshawar, Hyderabad and Quetta. Psychiatrists will identify potential participants and offer them information about the study. Those who agree will be contacted by the research team, pre-screened and provided detailed information about the study, including procedures protecting privacy and confidentiality. Potential participants will have a chance to ask questions prior to providing informed written consent. Participants will then undergo a screening assessment based on the eligibility criteria outlined in Appendix 1, followed by the baseline assessment. After that, an independent statistician will check the record of baseline measures and will randomise the participant to one of the two arms of the study. The participant will be contacted by the study coordinator at their recruitment centre within 1 week of randomisation to inform them about treatment allocation. The time and date of sessions will be set based on the participant's preference. Participants randomised to the intervention arm will be offered 12 weekly individual sessions. Each session will last for 60 min. All sessions will be delivered by a trained therapist, who will receive 2 months of training from senior therapists before starting the intervention. Assessments will be carried out at baseline and at 3, 6 and 12 months. The assessment scales will be administered in person and/or via secure videoconferencing software (an alternative to in-person assessment to allow for COVID-19 or travel restrictions) by trained research analysts masked to treatment allocation.

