### Sample size

From preliminary evidence collected during the pilot RCT,^24^ we estimated the mean time to recurrence as 10 weeks in the TAU group and 45 weeks in the CaPE group. This resulted in a hazard ratio of 4.51. For the purposes of the current study, we assumed a more conservative mean time to recurrence of 21.4 weeks for the TAU group. For a sample size of 240 (120 in each group), we would have more than sufficient power (0.91) to detect a low hazard ratio of 1.60, which approximately corresponds to a mean relapse time of approximately 34.2 weeks in the CaPE group, a difference that would be of clinical importance. The minimum detectable hazard ratio to attain 0.80 power is 1.49. To allow for a possible 20% attrition rate, we aim to recruit 300 participants in total. For within-subgroup analysis, the minimum detectable hazard ratio is 1.67 for larger groups (e.g. males, ~60% of the sample based on pilot-trial data) and 1.88 for smaller groups (e.g. females, ~40% of the sample based on pilot-trial data). For subgroups defined by medium cut-off points, the minimum detectable hazard ratio is 1.75. For the current design, we could only detect between-group differences in treatment effects with adequate power (0.80) when there are drastic group differences, for example a hazard ratio of 1.75 in one group and 3.5 in another. As the effectiveness of CaPE is not yet established, it is premature to further increase our sample size to power subgroup analyses. Nevertheless, preliminary subgroup analysis will inform power calculations for future studies.

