### Statistical analysis

The intention-to-treat principle will be used, with participants analysed according to their allocated group. Our primary outcome is time to recurrence observed within 12 months. The treatment effect will be evaluated using the Cox proportional-hazards model with treatment assignment as the primary predictor. Baseline measures of key clinical characteristics (duration of illness, number of previous episodes) and demographics (age, gender, self-reported biological sex) will be controlled in the model. The treatment effect will be illustrated by the estimated hazard ratio to relapse between the two groups. In addition, parametric survival analysis models^38^ will be employed when appropriate. In the widely used Weibull distribution case (for example), the parametric analysis will use a log-linear model on the scale parameter with treatment assignment as the primary predictor while controlling for the set of covariates described above. The regression coefficient on treatment assignment can be interpreted as the log hazard ratio between the two treatment conditions in terms of relapse. This will help estimate the mean time to recurrence for the two groups. As this is a multicentre trial, dependencies for participants from the same centre will be accounted for by including centre as a random effect.^25^ We will investigate levels of missing data, assumptions (e.g. missing at random) and predictors of missingness. Missingness will be addressed using multiple imputations, capitalising on fitting mixed models with maximum likelihood and appropriate sensitivity analyses.^39^ We will also conduct an exploratory mediation analysis to investigate the role of treatment adherence and bipolar disorder type (I or II) on 12-month outcomes. Statistical inference will be conducted using two-tailed tests with 0.05 as the level of significance and 95% confidence intervals with secondary outcomes adjusted for multiple comparisons as necessary. We will use the most appropriate analytic and graphical features of SPSS, STATA and R as relevant.

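### The only planned summary in weeks is a parametric mean time to recurrence with no stated truncation at 12 months; at the design values about 44% of the between-group difference in means lies beyond follow-up

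*Protocol article*

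**What the plan says.** All references are to the protocol article.

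- **Outcome and its window.** Outcome measures: "The primary outcome measure is time (in weeks) to recurrence of a mood (depressive/manic/hypomanic/mixed) episode". Statistical analysis: "Our primary outcome is time to recurrence observed within 12 months". Study procedures: "Assessments will be carried out at baseline and at 3, 6 and 12 months". Nothing is scheduled after month 12.
- **Main effect measure.** Statistical analysis: "The treatment effect will be illustrated by the estimated hazard ratio to relapse between the two groups". The hazard ratio comes from the Cox model.
- **Additional models.** Statistical analysis: "In addition, parametric survival analysis models^38^ will be employed when appropriate". The Weibull is given as an example. The paragraph then says: "This will help estimate the mean time to recurrence for the two groups".
- **Target effect in weeks.** Sample size: "we assumed a more conservative mean time to recurrence of 21.4 weeks for the TAU group", with a hazard ratio of 1.60 "which approximately corresponds to a mean relapse time of approximately 34.2 weeks in the CaPE group". The same sentence calls the difference clinically important.

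The Statistical analysis section gives no upper limit for the mean and names neither a restricted mean nor a median.

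**The concern.** A mean time to recurrence is the whole area under the recurrence-free curve. When some participants are still recurrence-free at the last visit, the area to the right of that visit has no data behind it. It is supplied by whatever distribution was fitted up to month 12 and is assumed to continue beyond it. The outcome is confined to 12 months, but the quantity in weeks attached to it is not.

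What is at stake is interpretation. The Discussion hopes to persuade guideline makers, clinicians and patients, and such readers will find a gain in weeks easier to quote than a hazard ratio. As planned, that figure would be partly an extrapolation, more so in the CaPE arm, and nothing in the text would say so.

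**Working it through.** **Inputs.** Means of 21.4 weeks (TAU) and 34.2 weeks (CaPE), HR 1.60, 120 analysed per group and stated power 0.91 (Sample size); two-sided alpha 0.05 and a 12-month window, taken as 52 weeks (Statistical analysis).

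**Step 1: which distribution the figures imply.** 34.2 / 21.4 = 1.598, which the article equates with HR 1.60. A ratio of means equals the hazard ratio under exponential times with unrestricted means. The article does not name the exponential, so this is an inference from its numbers.

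**Step 2: reproduce the stated power.** With 52 weeks of follow-up for everyone and a CaPE mean of 1.60 × 21.4 = 34.24:
- Expected events = 120 × [(1 − exp(−52/21.4)) + (1 − exp(−52/34.24))] = 120 × (0.912 + 0.781) ≈ 203.
- Schoenfeld: Φ(√203.15 × ln 1.60 / 2 − 1.96) = Φ(1.39) = 0.918.
- Freedman: Φ(√203.15 × 0.60/2.60 − 1.96) = Φ(1.33) = 0.908.
- If all 240 had an event, Schoenfeld would give 0.954.

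The stated 0.91 is reproduced with censoring at about 12 months and not without it. The power figure therefore already allows for the follow-up limit; the means in weeks beside it do not.

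**Step 3: split each mean at week 52.** For an exponential mean m, the recurrence-free share at week 52 is exp(−52/m), and the restricted mean is m × (1 − exp(−52/m)).

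| | TAU | CaPE | Difference |
|---|---|---|---|
| Unrestricted mean (weeks) | 21.4 | 34.2 | 12.8 |
| Recurrence-free at week 52 | 8.8% | 21.9% | |
| Restricted mean to week 52 | 19.5 | 26.7 | 7.2 |
| Part beyond week 52 (weeks) | 1.9 | 7.5 | 5.6 |

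Share of the difference beyond follow-up: 5.6 / 12.8 = 44%. The ratio of restricted means is 26.7 / 19.5 = 1.37, not 1.60, which confirms that the design means are unrestricted.

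**Step 4: sensitivity to the tail.** Hold the 52-week recurrence-free shares at 8.8% and 21.9% and vary a common Weibull shape. The range 0.6 to 1.5 is an assumption. Because ln(0.088)/ln(0.219) ≈ 1.60, the hazard ratio is the same in every row.

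| Shape | Difference in unrestricted means | Difference in restricted means to week 52 |
|---|---|---|
| 0.6 | 21.1 | 7.8 |
| 0.8 | 15.5 | 7.6 |
| 1.0 | 12.8 | 7.2 |
| 1.25 | 10.8 | 6.8 |
| 1.5 | 9.5 | 6.3 |

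The unrestricted difference more than halves across the range; the restricted one moves by 1.5 weeks.

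**Step 5: precision.** In simulated trials (120 per arm, exponential truth, no dropout), a Weibull fitted to each arm gave a mean difference of 13.1 weeks (SD 4.7). The Kaplan-Meier restricted mean difference was 7.3 weeks (SD 2.2).

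**The case against.** The strongest reply is that the mean has a small role. The hazard ratio is the named effect measure, parametric models are additional and conditional, the Weibull is only an example, and no test of a difference in means is planned. All of that stands, and it limits the weight of the point.

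A second reply is that the article is silent on the horizon and does not say that the mean runs past week 52. A fitted Weibull can yield a restricted mean, and an analysis plan that is not shown may set one. This has force for the analysis text. It has less for the Sample size section, where the means are unrestricted on the article's own arithmetic and carry the statement of clinical importance. A reader would naturally set the trial's mean in weeks against those two figures.

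A third reply is that means are an ordinary way to enter exponential rates into a power calculation. That is correct. A reader might infer that the power or sample size is therefore overstated. The documents do not support this: the stated power is reproduced only when censoring at about 12 months is already included.

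Finally, a restricted mean is not free of assumptions. The article allows for 20% attrition, so censoring or imputation assumptions remain; only extrapolation past week 52 is avoided. A simple two-group routine would also not carry over the planned covariates and centre random effect.

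**Conclusion.** The point holds as a minor one about the summary in weeks. Followed as written, the plan yields a figure that depends materially on the curve after follow-up ends. At the design values, 5.6 of 12.8 weeks (44%) lie beyond week 52, and the difference within follow-up is about 7.2 weeks.

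These sizes assume exponential times, implied but not named, and 12 months taken as 52 weeks. Other Weibull shapes change how much is extrapolated (in CaPE, from about 12% of the mean at shape 1.5 to 44% at shape 0.6), not whether it is. The shape would be estimated from the first 52 weeks, so the range in the second table shows sensitivity rather than a forecast.

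A reader might go further and infer that the primary analysis itself rests on extrapolation. It does not: the Cox hazard ratio, its test and the sample size stand as they are.

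**What to change.** - **Statistical analysis.** Name the difference in restricted mean recurrence-free time to 52 weeks, with a 95% CI, as the summary in weeks beside the Cox hazard ratio. Say whether it comes from Kaplan-Meier curves or from the fitted adjusted model, and how dropouts are handled.
- **Same section.** If an unrestricted parametric mean is also shown, label it as an extrapolation beyond month 12.
- **Sample size.** Add that HR 1.60 corresponds to about 7.2 weeks within the 52-week window (26.7 v 19.5), under exponential times.

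The cost is a few sentences and a little more analysis in software the article already names; design, data collection and sample size do not change. The stated gain in weeks becomes smaller, and the restricted mean still needs a censoring or imputation assumption.

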### The CaPE intervention

CaPE is a manualised intervention for bipolar disorder consisting of 12 one-to-one psychoeducation sessions, one session per week. The decision to deliver the intervention individually is based on our pilot study^24^ and takes into account local cultural norms and expectations regarding the delivery of mental healthcare. From our experience in large trials of psychosocial interventions in Pakistan, participants are uncomfortable sharing experiences of mental illness in group settings because of local beliefs and the stigma associated with mental illness. Each CaPE session (Appendix 2) lasts for approximately 1 h, beginning with a 20–30 min presentation on the topic of the session, followed by a related exercise (e.g. drawing a life chart or compiling a list of potential triggers for recurrence). The manual is a modified and culturally adapted version of the Barcelona Bipolar Disorders Program.^25^ Master's-level clinical psychologists will facilitate all sessions. Pakistan produces over 3000 Master's-level psychologists each year, and these clinicians are an underused resource, making it feasible and economically sustainable for them to deliver CaPE individually. The same psychologist will deliver all 12 sessions to ensure continuity. Psychologists will receive regular weekly supervision from local co-investigators to maintain fidelity.

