### Control condition (TAU)

Local medical, psychiatric and family medicine services provide routine care according to their clinical judgement and available resources. Treatment as usual (TAU) will be ascertained by the participant's treating physician. Research staff will record the nature and intensity of TAU delivered to each participant. In current practice, people with bipolar disorder are not routinely referred for any psychological therapies in Pakistan. TAU for the disorder in Pakistan largely comprises pharmacotherapy.

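### The planned model allows for clustering by centre only; if psychologists differ in effect, the standard error of the treatment log hazard ratio would be too small, so a therapist-clustered sensitivity analysis should be pre-specified

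*Protocol article*

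**What the plan says.** All places are in the Method of the protocol article.

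- **Statistical analysis.** "The treatment effect will be evaluated using the Cox proportional-hazards model with treatment assignment as the primary predictor". On dependence, "dependencies for participants from the same centre will be accounted for by including centre as a random effect". No therapist term, therapist-clustered variance or therapist sensitivity analysis is named. Inference uses "two-tailed tests with 0.05 as the level of significance".
- **The CaPE intervention.** CaPE consists of "12 one-to-one psychoeducation sessions, one session per week", and "The same psychologist will deliver all 12 sessions to ensure continuity". Each CaPE participant therefore belongs to one therapist.
- **Control condition (TAU).** "people with bipolar disorder are not routinely referred for any psychological therapies in Pakistan", and usual care is mostly drug treatment. TAU participants have no trial therapist.
- **Process evaluation.** Interviews are planned with every therapist in the trial, so there are several. Their number and caseloads are not given.
- **Sample size.** Power is 0.91 for a hazard ratio of 1.60 with 240 analysed participants, 120 per arm. No design effect is mentioned.

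**The concern.** Randomisation is 1:1 and stratified by site, so centre-level differences in recurrence fall on both arms and largely drop out of the comparison. A centre random intercept represents that shared component. A therapist effect is different, because it acts on CaPE participants only. Where a centre has one therapist, it is a centre-by-treatment effect; where a centre has several, it is a further level below centre. A shared centre intercept captures neither.

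If therapists vary, participants with the same therapist carry less independent information than the model assumes. The standard error of the treatment log hazard ratio is then too small, its confidence interval too narrow, and the power lower than stated. This matters because the article presents the trial as confirmatory and as a basis for rapid implementation. That use asks for inference beyond the particular psychologists employed.

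**Working it through.** **Inputs from the article.** 120 analysed per arm; mean time to recurrence 21.4 weeks (TAU) and 34.2 weeks (CaPE); hazard ratio 1.60; 12 months of follow-up, taken as 52 weeks; two-sided alpha 0.05.

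**Assumptions, not in the article.** Exponential times; K therapists with equal caseloads, K from 8 to 26; between-therapist SD s of 0.1 to 0.4 on the log hazard, in CaPE only. K = 13 corresponds to one therapist per recruitment site: "There are five recruitment sites in Karachi, three in Lahore and one each in Multan, Rawalpindi, Peshawar, Hyderabad and Quetta".

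**1. Reproduce the stated power.**
- Expected events: TAU 120 × (1 − exp(−52/21.4)) = 109.4; CaPE 120 × (1 − exp(−52/34.2)) = 93.8; total 203.2.
- Freedman: Φ(√203.2 × 0.6/2.6 − 1.96) = 0.908.
- Schoenfeld: 0.918.
- Exponential log hazard ratio: SE = √(1/109.4 + 1/93.8) = 0.1407, power = Φ(0.470/0.1407 − 1.96) = 0.916.

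The stated 0.91 is recovered with independent participants, so it contains no therapist design effect.

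**2. Type I error when therapist is ignored.** With no average effect, both arms expect 109.4 events. The model's variance is 2/109.4 = 0.01828; the actual variance is about 0.01828 + s²/K. The SE ratio is r = √(1 + (s²/K)/0.01828), and the actual alpha is 2 × (1 − Φ(1.96/r)).

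| K | s = 0.1 | s = 0.2 | s = 0.3 | s = 0.4 |
|---|---|---|---|---|
| 8 | 5.8% | 8.2% | 12.3% | 17.6% |
| 13 | 5.5% | 7.0% | 9.5% | 13.0% |
| 20 | 5.3% | 6.3% | 7.9% | 10.2% |
| 26 | 5.2% | 6.0% | 7.2% | 9.0% |

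Worked cell, K = 13, s = 0.3: s²/K = 0.00692; r = √(1 + 0.00692/0.01828) = 1.174; 1.96/1.174 = 1.669; alpha = 9.5%.

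**3. Simulation of the same set-up** (log-rank test ignoring therapist, 2,000 trials per cell), for s = 0.2/0.3/0.4:
- K = 8: 8.0/11.6/16.5%
- K = 13: 6.8/8.7/12.4%
- K = 20: 6.5/8.2/11.2%

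A second run gave 15.9% at K = 8, s = 0.4, so the formula overstates a little in that corner and about 16% is the better upper figure. At s = 0.1 simulation gave about 5.2% to 6.5% across 8 to 26 therapists.

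**4. Does adjusting for centre remove it?** A null simulation used seven centres of uneven size, a test stratified by centre, and 13 therapists. Rejection was 5.0% with no therapist variation, and 5.9%, 7.0%, 9.4% and 12.5% at s = 0.129, 0.183, 0.294 and 0.428 (intraclass correlations 0.01, 0.02, 0.05, 0.10). Adjusting for centre does not remove the problem.

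**5. Power with a correct standard error.** The variance at hazard ratio 1.60 is 1/109.4 + 1/93.8 + s²/K = 0.01980 + s²/K, and power is Φ(0.470/√variance − 1.96). This gives:
- no therapist variation: 0.916
- K = 26, s = 0.1: 0.911
- K = 13, s = 0.3: 0.820
- K = 8, s = 0.4: 0.654

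**The case against.** **Omission rather than error.** The quoted sentence deals with the multicentre structure and does not say that centre is the only random effect. Therapist terms and data fields are often left to an analysis plan, which is not at hand. This stands in part: nothing shows that therapist ID will go unrecorded. But the article does state how dependence is handled, and the structure it names misses the dependence that bears on the treatment contrast.

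**Conditional on therapist variation.** A reader might infer that the standard error is wrong and the 5% level exceeded as a matter of fact. The article does not support that. With no therapist variation nothing changes, and if CaPE affects nobody, therapists cannot differ in its effect and the test keeps its level. The inflation refers to a null effect averaged over therapists who differ. This stands, and the point is worded accordingly. Where effects do vary, the interval around the average effect is still too narrow.

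**Large assumed values.** An SD of 0.3 puts 95% of therapists between hazard multipliers of 0.56 and 1.80; an SD of 0.4, between 0.46 and 2.19. These are wide against a target hazard ratio of 1.60. CaPE is manualised, and its psychologists have Master's-level qualifications, two months of training and weekly supervision. This stands, and is why the range starts at an SD of 0.1.

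**Technical limits.** Most of the simulations use an unadjusted log-rank test rather than the planned covariate-adjusted Cox model. Exact cancellation of a shared centre intercept is a linear-model result; in a Cox model, conditioning on a frailty can move both the estimate and its standard error. Both remarks are fair, but the centre-stratified check shows that the one-arm effect survives adjustment for centre.

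**Conclusion.** The point holds in conditional form. The stated handling of dependence does not cover therapist clustering in the CaPE arm. If therapist variance is above zero, the standard error of the treatment contrast, not of the CaPE arm alone, is too small, and the stated power is optimistic.

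The direction is certain under that condition; the size is not. Over the assumed range it runs from negligible (about 5%) to material (about 16%), and the low end is plausible given the controls on delivery. Equal caseloads are assumed. The extreme of a single therapist per centre gave higher simulated rates (7.6% to 31.8% at intraclass correlations of 0.01 to 0.10), but nothing in the article suggests that one psychologist would treat all Karachi participants.

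A reader might also conclude that a therapist frailty must become the primary model. That goes too far: five of the seven centres plan 20 participants each, about 10 in CaPE, perhaps with one therapist, and a variance estimated from few small clusters is imprecise. A pre-specified sensitivity analysis is the proportionate step.

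**What to change.** 1. Record therapist ID for each CaPE participant during delivery, since it may be hard to recover later.
2. Pre-specify a sensitivity analysis of the primary Cox model with therapist clustering in the CaPE arm only. Use either a partially nested frailty or a therapist-clustered robust variance with each TAU participant as a singleton. Report its hazard ratio and interval next to the primary ones.
3. State in the Sample size section that 0.91 power assumes no variation between therapists.

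The cost is one data field and a few sentences of plan text. The statistical downside is a somewhat wider interval, and an imprecise therapist variance where a centre has only one or a few therapists; the report should say so.

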#### Randomisation and masking

Participants will be randomised using a block randomisation technique in a 1:1 allocation to CaPE or TAU. Randomisation will be computer generated and use a random permuted block method with variable block sizes. The sample will be stratified by site, bipolar type (I or II) and self-reported biological sex, given the potential differences in recurrence rates in these groups. In line with best practice in RCTs, we have not included further stratification variables.^38^ We will assess other potential prognostic characteristics (age, duration of illness, number of previous episodes, gender) in our *a priori* subgroup analyses.

This will be an assessor-masked RCT. Owing to the nature of the interventions, clinicians in participating centres and the participants themselves cannot be masked to treatment allocation. Before assessments, participants will be asked not to reveal any information about treatment to assessors. To avoid unmasking, outcome assessors will be located separately from treatment providers, and we will assign new outcome assessors in cases of unintentional unmasking. Statistical analysis will be partially masked (knowing treatment groups, but not what each group is). The intention-to-treat analysis plan will help reduce the effect of attrition bias. Finally, registration on Clinicaltrials.gov and publication of results regardless of the outcome will both minimise reporting bias.

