#### Subgroup analyses

Subgroup analysis will be carried out with respect to age, duration of illness, number of previous episodes, gender and self-reported biological sex by adding a treatment with covariate interaction into the primary analysis model.

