### Eligibility criteria

Inclusion criteria

- Adult out-patients age 18 years and above
- Diagnosis of DSM-5 bipolar disorder (both bipolar disorder I and bipolar disorder II), currently in remission, confirmed by Structured Clinical Interview for DSM-5 (SCID)
- Currently euthymic (17-item Hamilton Rating Scale for Depression score <8 and Young Mania Rating Scale score <8)
- Able to give informed consent
- On stable psychiatric medication regimen for at least 3 months
- Resident of the trial catchment area.

Exclusion criteria

- Active substance use disorder, based on DSM-5 criteria
- Currently experiencing recurrence (mania, hypomania, mixed or depressive
- Active suicidal ideation
- Unstable residential arrangements that reduce likelihood of being available for the duration of trial.

## Appendix 2

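### Bipolar type is fixed before randomisation and so cannot mediate the effect of CaPE, yet it is named in the mediation analysis and is absent from the planned interaction tests

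*Protocol article*

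**What the plan says.** Under Statistical analysis, the protocol article announces an "exploratory mediation analysis to investigate the role of treatment adherence and bipolar disorder type (I or II) on 12-month outcomes". Both variables are named under the one method, and nothing separates their roles.

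Other sections show when bipolar type becomes known:

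- Appendix 1 (Eligibility criteria) makes a SCID-confirmed diagnosis of bipolar I or II an inclusion criterion.
- Study procedures puts screening and baseline assessment first. Only then does it say that "an independent statistician will check the record of baseline measures and will randomise the participant to one of the two arms".
- Randomisation and masking states: "The sample will be stratified by site, bipolar type (I or II) and self-reported biological sex, given the potential differences in recurrence rates".

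Tests of differing treatment effect are set out under Subgroup analyses. They are to be done "with respect to age, duration of illness, number of previous episodes, gender and self-reported biological sex", and the method is "by adding a treatment with covariate interaction into the primary analysis model". Bipolar type is not in that list. It is also absent from the shorter list of a priori subgroup variables under Randomisation and masking, and from the covariates of the primary Cox model under Statistical analysis.

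**The concern.** A mediator lies on the path from treatment to outcome, so treatment must be able to change it. A diagnosis made before allocation does not meet that condition. It can predict the outcome, or it can modify the treatment effect, but it cannot carry that effect.

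Two things follow. First, the mediation analysis of type estimates a quantity known in advance to be zero. A null result could be misread as evidence that type is irrelevant to how CaPE works, and a non-null one would be an artefact. Second, the useful question, whether the hazard ratio differs between bipolar I and II, has no planned analysis in this document, although type was thought important enough to stratify on. If an interaction with type were added after the data are seen, it would be post hoc.

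**Working it through.** **Can treatment change the variable?** Setting the sections side by side:

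| Variable | When it is fixed or measured | Can allocation change it? | Possible role |
|---|---|---|---|
| Treatment adherence (MMAS-4, Appendix 3) | Baseline and months 3, 6 and 12 | Yes | Mediator |
| Bipolar type (Appendix 1; Randomisation and masking) | Screening, before allocation | No | Covariate or effect modifier |

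**Indirect effect.** In the usual product form, indirect effect = a × b, where a is the effect of treatment on the candidate mediator and b is the effect of that variable on the outcome given treatment. For bipolar type, each participant's value is the same under CaPE and TAU, so the true a = 0 and the true indirect effect is 0 × b = 0, whatever b is.

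The *estimate* of a need not be exactly zero. Seven centres × 2 types × 2 sexes gives 28 strata, or 300/28 ≈ 10.7 participants each. If site means the recruitment sites listed under Study procedures (5 + 3 + 5 = 13), there are 13 × 2 × 2 = 52 strata, or 300/52 ≈ 5.8 each. Incomplete blocks in small strata, and the 20% attrition allowed for under Sample size, can leave some imbalance in type between the arms. That imbalance is the only source of a non-zero result.

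**Is the moderation question planned elsewhere?** The two patient-level stratification factors are type and sex, and both were chosen on the same stated ground. Sex is in the Subgroup analyses list; type is not. No interaction with type appears in any other section.

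**Does the repair disturb the design?** The article's own power figure was reproduced first. Inputs from Sample size: means of 21.4 and 34.2 weeks, 120 per arm, HR 1.60; from Statistical analysis: two-sided 0.05, and 12 months taken as 52 weeks. Exponential times are assumed.

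- Events = 120 × (1 − exp(−52/21.4)) + 120 × (1 − exp(−52/34.2)) = 109.4 + 93.8 ≈ 203.
- Schoenfeld: Φ(√203.2 × ln 1.60 / 2 − 1.96) = 0.918.
- Freedman: Φ(√203.2 × 0.60/2.60 − 1.96) = 0.908.
- Stated: 0.91. Recruitment: 240/(1 − 0.20) = 300, as stated.

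Moving type from mediation to interaction alters none of these inputs.

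**How informative would the interaction test be?** The article does not give the split between bipolar I and II, so a range is needed. Take the article's own example of a large difference, HR 1.75 in one group and 3.5 in the other, with 240 analysed. Then power = Φ(ln 2 / SE − 1.96), with SE = √(4/e₁ + 4/e₂) and e₁, e₂ the events in the two groups.

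| Assumed split (larger group at HR 1.75) | e₁ | e₂ | SE | Power |
|---|---|---|---|---|
| 50:50 | 99.8 | 84.8 | 0.295 | 0.65 |
| 70:30 | 139.7 | 50.9 | 0.328 | 0.56 |
| 80:20 | 159.6 | 33.9 | 0.378 | 0.45 |

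The article associates this contrast with power of 0.80, without giving its method. The approximation here is used only to show that the test would be exploratory.

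**The case against.** The strongest reply is that the sentence never calls bipolar type a mediator. It speaks of the role of adherence and type within a mediation analysis, which would fit a moderated-mediation model with adherence as mediator and type modifying a path. That may have been the intent, and a condensed article need not give the model specification. But the text names one method for both variables and plans no interaction with type, so a reader cannot recover that meaning. If it was intended, a short clarification settles it.

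A second reply is that stratifying on a factor does not oblige anyone to test it as a subgroup. The stated reason for stratifying concerns recurrence rates, which is prognosis rather than differing treatment effect. This stands in part: the omission contradicts no statement in the article, and adding type is a recommendation. What supports it is the uneven handling of type and sex.

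A third reply is that the analysis is exploratory and the interaction test weak. Both are true and limit the weight of the point. They do not make a structurally null quantity informative, and the article already accepts low power for its other subgroup analyses.

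Three stronger inferences are tempting and are not supported:

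- *The estimated indirect effect will be zero whatever the data.* Only the true effect is zero; the estimate can depart from it through chance imbalance or attrition.
- *A pre-specified moderator test is lost.* None was planned for type, so none is lost.
- *Effect modification by type will never be examined.* The statistical analysis plan is not available, so one can say only that this document does not plan it.

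**Conclusion.** The point holds as a wrongly stated method with moderate weight. Naming a pre-randomisation stratification factor in a mediation analysis targets an indirect effect whose true value is zero by design. The answerable question about type is not planned in this document. The conclusion rests on the article's own sequence of diagnosis, stratification and randomisation, and on no numerical assumption. The primary test, the event count and the recruitment target are not materially affected. The only figures that depend on assumption are the interaction powers, roughly 0.45 to 0.65 over the assumed splits for a twofold ratio of hazard ratios. They show that an added test by type could generate hypotheses but would be unlikely to settle the matter.

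**What to change.** Three edits to the article's analysis text:

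1. In Statistical analysis, restrict the exploratory mediation analysis to treatment adherence. Alternatively, state explicitly that bipolar type enters it only as a moderator.
2. In Subgroup analyses, add bipolar type as an exploratory treatment-by-type interaction. Fit it in a separate model that also contains the type main effect, so that the primary treatment estimate is not redefined.
3. In Statistical analysis, add bipolar type to the primary Cox covariates, because it is a stratification factor and is at present missing from them.

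The data are already collected at screening. The cost is the rewording and one more exploratory interaction test with low power, which should be reported as such with its confidence interval. The edits should be made before any comparison by arm is seen.
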